### Concomitant and forbidden drugs

If participants experience unbearable cough at night, taking one capsule acetylcysteine is permitted; this antitussive will be delivered to the patients along with the MMDT or placebo granules. If this does not improve the cough, the participant will visit the K-CTC for examination and appropriate management. The participants will be asked to record whether they take the antitussive agent or not. Other drugs that alleviate cough—such as other antitussives, glucocorticoids, leukotriene receptor antagonists, anticholinergics, short-acting β2 agonists, long-acting β2 agonists, and antihistamines—are prohibited. Drugs which are not related to cough symptoms will be permitted. The name, duration, and dosage of any other drugs taken will be recorded in the case report forms.

### Outcome measures

#### Primary outcomes

The primary outcome is the cough diary score at week 4. The cough diary score on the last day of the 1-week run-in period will be taken as the baseline score of participants who will be enrolled and randomized for the trial.

The cough symptom scoring recommended by Spector et al. will be used in this study [27]. The daily cough diary consists of two parts: daytime (08:00–20:00) and nighttime (20:00–08:00) cough symptoms. Patients will be required to evaluate their symptoms twice per day (daytime and nighttime). Daytime cough symptoms will be graded from zero to five as follows: 0—no cough; 1—cough for one short period; 2—cough for two or more short periods; 3—frequent coughs that did not interfere with usual daytime activities; 4—frequent coughs that did interfere with usual daytime activities; and 5—distressing coughs for most of the day. Nighttime cough symptoms will be graded from zero to five as follows: 0—no cough during the night; 1—cough on waking only; 2—waking once or early precisely because of cough; 3—waking frequently due to cough; 4—wakefulness for most of the night due to cough; and 5—distressing coughs preventing sleep. The total cough score (from 0 to 10) is the sum of the daytime and nighttime cough symptom scores.

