### Participants

#### Inclusion, exclusion, and withdrawal criteria

The inclusion criteria are: (1) age between 19 and 75 years; (2) chronic cough that has lasted more than 8 weeks; (3) dry cough (sputum frequency of 5 or fewer times per day, and sputum volume less than 10 ml per day, on the basis of the Sputum Severity Evaluation Standard of the Korean Ministry of Food and Drug Safety); (4) provision of written informed consent.

The exclusion criteria are: (1) abnormal pulmonary function test (forced vital capacity, or forced expiratory volume in 1 s, < 80 % of predicted); (2) abnormal chest X-ray; (3) acute respiratory disease, including upper respiratory tract infection, during the previous 4 weeks; (4) chronic pulmonary diseases (COPD, idiopathic pulmonary fibrosis, bronchiectasis, etc.) during the previous 2 years; (5) diagnosis of malignant tumor during the previous 5 years; (6) history of smoking (≥20 packs [400 cigarettes] during the participants’ lifetime); (7) treatment taking an angiotensin-converting-enzyme inhibitor at present or during the previous 4 months; (8) current or the precious 2-week use of antitussive drugs, glucocorticoids, leukotriene receptor antagonists, anticholinergic drugs, long-acting β2 agonists or any herbal medication; (9) antihistamine treatment during the previous 3 days; (10) aspartate aminotransferase (AST) or alanine aminotransferase (ALT) levels at least twofold higher than the upper normal limit, or a serum creatinine levels at least 1.2-fold the upper normal limit; (11) a mean cough diary score of less than 2 during the 1-week run-in period; (12) fewer than 10 entries in the cough diary during the 1-week run-in period; (13) pregnancy or breastfeeding; (14) illiteracy or cognitive impairment; (15) unsuitability as judged by the investigators.

The rejection and withdrawal criteria are: (1) treatment that might influence the results of the trial without the agreement of an investigator; (2) use of forbidden drugs, such as antitussives, glucocorticoids, leukotriene receptor antagonists, anticholinergics, and long-acting β2 agonists; (3) participants not following the protocol, or taking < 80 % of the prescribed doses; (4) a serious adverse event (SAE) during the trial; (5) voluntary withdrawal from the trial; (6) unsuitability as judged by the investigators.

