#### Placebo

The control group will receive placebo granules (3 g/pouch, 3 times per day—before each meal—for 4 weeks). The placebo was manufactured by the Jeonnam Bioindustry Foundation Food Research Center (JBF), following the placebo guidelines of the Korean Ministry of Food and Drug Safety. The granules do not contain any active ingredients, but are similar in appearance, taste, and scent to the MMDT granules.

All products were packaged by JBF (Naju, Republic of Korea). Either Forty-two MMDT or placebo pouches will be provided to each randomized participant at visit 1 (week 0 ± 3 days) and visit 2 (week 2 ± 3 days). The products will be stored at the K-CTC clinical research pharmacy in Kyunghee University Korean Medicine Hospital, and an independent and trained pharmacist will manage all procedures associated with the drugs. The study process is outlined in Table 1.

**Table 1 Tab1:** Study process: treatment and outcome measurements

Activity	Screening	Visit 1	Visit 2	Visit 3	Follow up
Time schedule	-Week 1	Baseline	Week 2	Week 4	Week 6
Window visit		±3 days	±3 days	±3 days	±3 days
Informed consent	X				
Demographics	X				
Cough symptom check	X				
Medical history	X				
Smoking history	X				
Medication history	X				
Safety test	X	X		X	
Chest X-ray	X				
Pulmonary function test	X				
Safety test	X				
Methacholine bronchial challenge test^a^	X				
Nasal endoscopy^a^	X				
Distribute cough diary card	X	X	X	X	
Randomization		X			
Height/weight/body mass index		X			
Vital sign		X			
Cough diary score		X	X	X	X
Cough visual analogue score		X	X	X	X
Leicester cough ques-tionnaire Korean versi- on		X		X	X
Pattern identification for chronic cough question-naire		X		X	
Cold-Heat pattern questionnaire		X		X	
Yin deficiency scale		X		X	
Hematological biomarker		X		X	
Immunologic biomarkers		X		X	
Investigational Produce		X	X		
Compliance			X	X	
Adverse events investi-gation			X	X	
Concomitant therapy eva- luation	X	X	X	X	

^a^The test will be performed as needed, according to the judgment of the investigator

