### Statistical analysis

Descriptive statistics will be used for continuous variables, and frequencies for categorical variables. The “last observation carried forward” (LOCF) principle will be used to compensate for missing data. The LOCF principle involves replacement of missing data with the last observed value to obtain a complete database.

When the assumption of normality is satisfied will a *t*-test be used to compare the two groups in terms of the primary outcome (mean cough diary score at week 4). Otherwise, the Mann–Whitney *U*-test will be used. Other continuous variables, such as mean efficacy measurements (cough VAS score or LCQ scores), safety tests (AST, ALT, ALP, TB, GGT, BUN, creatinine, sodium or potassium levels), and biomarkers will be analyzed using the same statistical methods. Associations between the MMDT responders and non-responders with regard to each identified pattern will be estimated using a logistic regression model, which will be adjusted for covariates. All data will be analyzed using SPSS™ for Windows software. The level of significance will be set at a two-sided P value of 0.05.

We, along with a professional statistician, will perform the data analysis for the results.

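### Baseline cough score rests on one diary day although a full week is recorded, and the week-4 primary score is not tied to a day or an averaging window

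*Protocol article*

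**What the plan says.** The Primary outcomes section describes a diary with two parts: "Patients will be required to evaluate their symptoms twice per day (daytime and nighttime". The two halves are summed to a daily total of 0 to 10.

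- **Primary outcome, Primary outcomes section:** "The primary outcome is the cough diary score at week 4". No day or window is named.
- **Primary outcome, Statistical analysis section:** the groups are compared on "the primary outcome (mean cough diary score at week 4". The sentence does not say over what the mean is taken.
- **Baseline, Primary outcomes section:** "The cough diary score on the last day of the 1-week run-in period will be taken as the baseline score".
- **Eligibility, exclusion criteria:** "a mean cough diary score of less than 2 during the 1-week run-in period" excludes a patient, as does having "fewer than 10 entries in the cough diary during the 1-week run-in period".
- **Primary test:** a t-test, or a Mann–Whitney test if normality fails, on the week-4 score, with no baseline term.
- **Responder:** a participant in the MMDT arm whose diary score falls by 75% after 4 weeks. All others in that arm are non-responders. Responder status is then related to the traditional-medicine patterns by logistic regression.

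**The concern.** The plan relies on the weekly mean to decide who enters, then uses one of the same seven days as the reference for change. One daily total is a whole number from 0 to 10 and carries all of that patient's day-to-day variation. A percentage change divides by it, so the error matters most when the value is small. Selecting on the weekly mean does not prevent a low last day.

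The second issue is the primary outcome itself. A daily diary allows at least two readings of a score at week 4: one day's total, or a patient's mean over the last treatment week. They have different variances and therefore different power at the planned sample size. The Sample size calculation section gives the effect size only in SD units and does not say which kind of score the SD belongs to.

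**Working it through.** **Inputs from the protocol article:** adjusted effect size 0.85, two-sided alpha 0.05, power 80%, 20% dropout, 1:1 allocation, 58 participants (Sample size calculation and Statistical analysis); 7 run-in days with two entries each; 4 weeks (28 days) of treatment. **Not given:** the SD of the diary score and the correlation between days. Both are assumed below.

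**1. The plan's own figure.** A two-sample t-test (noncentral t) with d = 0.85 needs 22.73, so 23 per arm. Then 23 / 0.8 = 28.75, so 29 per arm and 58 in total. This matches the article. Power with 23 per arm is 80.5%.

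**2. One day against a 7-day mean.** With equal correlation ρ between any two days, the variance of a 7-day mean relative to one day is (1 + 6ρ)/7:
- ρ = 0.4: 3.4/7 = 0.49
- ρ = 0.6: 4.6/7 = 0.66
- ρ = 0.8: 5.8/7 = 0.83

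**3. Power with 23 evaluable per arm**, holding the difference in points fixed:

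| ρ | 0.85 on single-day SD, 7-day mean analysed: d = 0.85/√ratio | Power | 0.85 on weekly-mean SD, one day analysed: d = 0.85·√ratio | Power |
|---|---|---|---|---|
| 0.4 | 1.22 | 98% | 0.59 | 50% |
| 0.6 | 1.05 | 94% | 0.69 | 63% |
| 0.8 | 0.93 | 87% | 0.77 | 73% |

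If the score analysed is of the same kind as the score behind the 0.85, power stays at 80%.

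**4. Zero or near-zero baseline.** A made-up example: run-in daily totals of 3, 3, 3, 3, 2, 2, 0 have mean 16/7 = 2.29, so the patient passes the mean-score criterion, yet baseline is 0 and a percentage decrease cannot be computed. For a baseline of 1, 2 or 3, a 75% fall means a score of at most 0.25, 0.5 or 0.75, so on a whole-number score only 0 qualifies.

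How often this happens depends on assumed values. I simulated daily totals with SD 1.8 and mean 4 to 5, rounded and limited to 0–10, run-in mean at least 2, ρ from 0.4 to 0.8. The last day differed from the weekly mean by at least 1 point in 24–48% of eligible patients. The chance of at least one zero baseline among the 29 MMDT participants, the only arm in which responders are defined, was about 1–35%.

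**5. Share of days used.** Baseline uses 1 of 7 run-in days. The week-4 score uses 1 of 28 treatment days if one day is meant, or 7 of 28 if the last week is averaged.

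**The case against.** The case for leaving the text alone has real strength, and several stronger readings that a reader might infer do not hold.

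- **That the two sections contradict each other.** They do not demonstrably do so. The Primary outcomes section never says a single day is meant. The word *mean* in the Statistical analysis section may be only the group mean, as it most naturally is for the VAS and LCQ-K scores elsewhere in the article. On the other side, the exclusion criteria use *mean cough diary score* for a patient's weekly mean. The wording is ambiguous, no more.
- **That baseline noise costs power or weakens adjustment in the primary test.** It cannot, because baseline does not enter that test.
- **That averaging certainly raises power from 80% to 94%.** This needs both a correlation of 0.6 and an effect size on the single-day SD. The article supports neither.
- **That the daily data are thrown away.** Run-in days decide eligibility, and Table 1 lists diary scores at weeks 2 and 6. A last-week mean would also leave 21 of 28 treatment days out of the primary outcome.
- **That the week-4 score may be taken after supply ends.** Two packs of 42 at 3 a day last 28 days and visit 3 may be 3 days late, but nothing says the score is the entry of the visit day.
- **That the endpoint can be chosen after unblinding.** A full protocol or analysis plan, not shown here, may fix the window.

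It is also fair that responder status is a secondary, exploratory analysis, and that a zero-baseline participant would fall among the non-responders by default. What remains is that the one-day baseline is an explicit choice in this document, so no unseen plan excuses it, and that the sole primary outcome can be read in two ways here.

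**Conclusion.** The point holds in two parts of different weight.

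First, the one-day baseline is stated outright and is a poor choice given the data already collected. Its effect is confined to the baseline description, the MMDT responder split and any change score. In the responder split it can misclassify patients and can leave the percentage undefined. The 1–35% chance of at least one zero baseline rests on an assumed SD, mean and correlation and is illustrative.

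Second, the day or window of the week-4 score is unresolved in this article. Over assumed correlations of 0.4 to 0.8, the reading chosen moves power from the planned 80% up to 87–98% or down to 50–73%, depending on which SD the 0.85 refers to. These figures show sensitivity and do not estimate the trial's actual power. The sample size of 58 is arithmetically correct on its stated inputs.

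**What to change.** Use one definition in the Primary outcomes, responder and Statistical analysis sections:

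- **Baseline:** each patient's mean daily total (0–10) over the 7 run-in days, used for the baseline description and the responder definition.
- **Primary outcome:** each patient's mean daily total over days 22–28, counted from first dose and not from the visit date.
- **Minimum entries:** the number of days needed for each mean to be valid, and how a day with only one of its two entries is handled.
- **Sample size section:** whether the 0.85 is in units of a single-day SD or of an averaged-score SD.

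If a full protocol or analysis plan already fixes the week-4 window, align the article's wording with it and change only the baseline. Recruitment has started, so the change should be dated and made before unblinding. The cost is wording: every entry is already being collected. The one downside is the extra rule for missing half-day entries.

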#### Secondary outcomes

##### Cough visual analog scale

The cough VAS is an overall rating scale for cough frequency and severity ranging from 0 (no cough) to 10 (unbearable cough). The scale will be checked at baseline, and at weeks 2, 4, and 6 (follow-up visit). The cough VAS mean scores will be recorded at weeks 2, 4, and 6.

##### The Leicester Cough Questionnaire (Korean version)

The Leicester Cough Questionnaire (LCQ) is widely used to measure quality of life in cough patients. It was developed by Birring [28], and has been validated in several languages, including Korean (LCQ-K) [29]. The LCQ comprises three domains: physical, mental, and social quality of life; a total of 19 items are scored on 7-point Likert scales. A higher score indicates a more healthy state. Several studies [2, 30, 31] have demonstrated a correlation between cough symptom severity and LCQ score. At week 4, we will compare the MMDT and placebo groups in terms of mean LCQ-K scores.

##### Pattern Identification for Chronic Cough Questionnaire

The Pattern Identification for Chronic Cough Questionnaire (PICCQ) is used to identify patterns in chronic cough patients. We developed this questionnaire using the Delphi method [32], and conducted clinical research to confirm its validity and reliability. The PICCQ consists of four patterns: wind-cold, phlegm-turbidity, fire-heat, and deficiency (lung deficiency and kidney yang deficiency). The PICCQ comprises 38 items scored on 5-point Likert scales. A patient’s pattern is calculated by summing the scores of each item. We will investigate the chronic cough pattern distribution in chronic dry cough patients, as well as the correlation between chronic cough pattern and the efficacy of MMDT.

##### Cold-Heat Pattern Questionnaire

We will use the validated Cold-Heat Pattern Questionnaire, which consists of 20 symptom items (10 items to assess cold pattern and 10 to assess heat pattern) [33]. Each item requires only a “yes” or “no” response depending on the patient’s tendencies during the previous week. The total numbers of items that a participant responds ‘yes’ will be the cold or heat pattern score, respectively, for the responder. We will investigate the Cold-Heat Pattern in chronic dry cough patients, as well as the correlation between the cold-heat pattern scores and the efficacy of MMDT.

##### Yin Deficiency Scale

We will use the validated *yin* deficiency scale developed by Park [34]. This questionnaire consists of 27 items, each of which uses a 7-point Likert scale; the cut-off point was defined as 10 points. We will use the *yin* deficiency scale to evaluate chronic dry cough patients, as well as to investigate the correlation between the *yin* deficiency pattern and the efficacy of MMDT.

### Biomarkers

Biomarkers that reflect chronic cough and airway inflammation [35] will be evaluated. These include blood neutrophils, eosinophil counts, serum immunoglobulin E levels, sputum eosinophilic cationic protein levels, and proinflammatory cytokines such as tumor necrosis factor alpha, interleukin (IL)-4, IL-5, IL-8, IL-10, and IL-13.

### Adverse event reporting

An adverse event (AE) is an undesirable, unintended sign, symptom, or disease that does not necessarily have a cause-and-effect relationship with the intervention evaluated in a clinical trial. We will carry out continuous monitoring of AEs and make any decision in this regard on the basis of both objective and subjective signs, as well as blood test results. Appropriate measures will be taken immediately to minimize any SAEs.

### Safety outcomes

Safety will be investigated using adverse reaction reports and clinical laboratory tests; namely, liver function tests (AST, ALT, alkaline phosphatase [ALP], total bilirubin [TB], and γ-glutamyltranspeptidase [GGT] levels), renal function tests (blood urea nitrogen [BUN] and creatinine levels), and serum sodium and potassium levels. All women of childbearing age will also undergo human chorionic gonadotropin testing.

### Sample size calculation

We referred a randomized controlled trial (RCT) that was conducted to demonstrate the clinical efficacy of a herbal medication for the patients with cough variant asthma (CVA) [36]. It was inevitable because no RCTs have been carried out that address the comprehensive chronic cough symptom using a herbal mediation. Furthermore, the main manifestation of CVA is cough lasting more than 8 weeks without any abnormal pulmonary functions; this is very similar to clinical characteristics of the eligible participants recruited in this study.

Using a cough diary score, the CVA study compared the efficacy of a herbal medicine with that of standard therapy (leukotriene receptor antagonist combined with methylxanthine) for 2 weeks. The calculated effect size was 0.699 (α = 0.05, 1-β = 0.8, 2-tailed test). Because of the discrepancy in comparators and study duration between the previous and planned studies, we determined to eliminate the effect of standard therapy and add the effect of longer treatment duration; this resulted in an adjusted effect size of 0.85. Assuming a 20 % dropout rate, and an allocation ratio of 1, we have calculated the necessary sample size to be 58 participants (29 in each group). The above calculations were performed using G*Power™ software (ver. 3.1.9.2) for Mac.

### Statistical analysis plan

Data entry and management will be completed by an independent data administrator to ensure data accuracy. We will analyze the efficacy and safety of MMDT using the “intent-to-treat” (ITT) principle. Subordinately, we will also present the results of the analysis based on the “per protocol” principle.

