#### Patient groups for data analysis

##### Intent-to-treat population

The ITT population will include all participants treated with at least one dose of the study drug and who keep and return a daily cough diary for at least one day of recordings.

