##### Per-protocol population

The per-protocol population will include patients who take more than 80 % of the prescribed doses of the study drug, fill in the daily cough diary on 80 % of the study days, and return their diary to the researchers.

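### Safety is analysed in an ITT population that requires a returned cough diary, so a treated participant with a reported adverse event and no returned diary can be left out

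*Protocol article*

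**What the plan says.** The section Statistical analysis plan puts both kinds of outcome under one principle: "We will analyze the efficacy and safety of MMDT using the “intent-to-treat” (ITT) principle". The section Intent-to-treat population, which follows, defines the set. A participant must have been dosed at least once and must also be among those "who keep and return a daily cough diary for at least one day of recordings", so a returned diary is required as well as a dose.

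Two other groupings are defined. The per-protocol population adds a compliance threshold and asks participants to "fill in the daily cough diary on 80 % of the study days, and return their diary to the researchers". The responder and non-responder groups split the MMDT arm by change in diary score and do not compare arms. No set is defined by treatment alone.

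The safety data do not come from the diary. The section Safety outcomes names event reports and laboratory tests as the sources, and the section Adverse event reporting provides for continuous monitoring with no diary condition.

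**The concern.** Returning a diary is a condition about having efficacy data. It says nothing about whether a participant was exposed to the product or was harmed by it. Used as an entry condition for safety results, it can remove someone who was dosed and whose event is already on file.

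Whether a diary comes back may also be linked to harm. Table 1 distributes a diary card at visit 1 and places the next visit at week 2, so a participant who stops in between and does not come back may leave no on-treatment card. The withdrawal criteria also list "a serious adverse event (SAE) during the trial", so the most serious events lead to withdrawal under the plan itself.

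Safety is half of the stated objective. With 29 participants per arm, losing even a few events would visibly change the reported rate. If early stopping were more common in one arm, it would also change the comparison.

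**Working it through.** **1. The plan's own figure.** Inputs from the section Sample size calculation: effect size 0.85, two-sided α = 0.05, power 0.80, 20% dropout, 1:1 allocation.

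- Two-sample t-test (noncentral t): 22.73, rounded up to 23 per arm.
- Dropout: 23 / (1 − 0.20) = 28.75, rounded up to 29 per arm, 58 in total.

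The stated 58 reproduces. It is not in dispute and serves only to size the group at risk.

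**2. How many could be lost.** Planned dropout per arm is 0.20 × 29 = 5.8, about 6. If every dropout returned no qualifying diary, the safety denominator would fall from 29 to 23. If every dropout returned one, it would stay at 29. The documents do not say how many dropouts would return no diary or how many would have an event, so 0 to 6 per arm is an assumption.

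**3. Effect on a reported rate.** Take one arm of 29 treated. Let k participants have a reported event and return no qualifying diary, and let m of those retained have an event.

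- All treated: (m + k) / 29
- ITT as defined: m / (29 − k)

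| m | k | All treated | ITT as defined |
|---|---|---|---|
| 0 | 1 | 1/29 = 3.4% | 0/28 = 0% |
| 0 | 3 | 3/29 = 10.3% | 0/26 = 0% |
| 0 | 6 | 6/29 = 20.7% | 0/23 = 0% |
| 4 | 0 | 4/29 = 13.8% | 4/29 = 13.8% |
| 4 | 1 | 5/29 = 17.2% | 4/28 = 14.3% |
| 4 | 3 | 7/29 = 24.1% | 4/26 = 15.4% |
| 4 | 6 | 10/29 = 34.5% | 4/23 = 17.4% |

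The values of m and k are illustrative.

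**4. Direction.** The reported rate falls when events are more frequent among those excluded than among those retained. It rises in the opposite case: if the 6 excluded had no events and m = 4, 4/29 = 13.8% would be reported as 4/23 = 17.4%. A downward bias is therefore the concern when stopping is linked to harm, but it is not guaranteed.

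**5. Comparison of arms.** Suppose one arm has m = 4 and k = 3, and the other has m = 4 and k = 0. Among all treated the difference is 24.1% − 13.8% = 10.3 percentage points. In the ITT set as defined it is 15.4% − 13.8% = 1.6 points. The same loss in both arms would distort the difference less.

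**6. Which diary counts.** The exclusion criteria rule out anyone with "fewer than 10 entries in the cough diary during the 1-week run-in period", so every properly enrolled participant already has a run-in diary with more than one day of entries. If that diary satisfies the ITT condition, k = 0 for everyone and the clause excludes nobody. If the clause is meant to have an effect, it must refer to a diary kept on treatment. The definition does not say.

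**The case against.** The strongest reply is that the definition, read literally, loses nobody. It sets no period for the diary, cards are handed out from screening, and eligibility depends on run-in entries. On that reading there is no bias. This stands as a limit on the claim. It does not rescue the text, because it leaves the diary clause with nothing to do.

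Second, a reader might infer that any treated participant who leaves early with an adverse event disappears from the safety results. The documents do not support that. One recorded day on a returned diary is enough to stay in. An event that is never reported to the site is lost whatever set is used.

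Third, a reader might take the planned 20% dropout to show that about 6 per arm would be excluded. It does not: that figure covers all dropout and says nothing about diary return. It gives an upper end for an assumed range.

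Fourth, the laboratory comparisons are barely touched. Table 1 places the only post-baseline safety test at visit 3, so someone who has left before then has no observed on-treatment value in any set. The exposure is mainly in the adverse event results.

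Finally, a reader might infer from "Safety will be investigated using adverse reaction reports and clinical laboratory tests" that only causally related events will be counted. The documents do not support that either. The abstract says adverse events will be reported, Table 1 schedules their investigation, and the section Adverse event reporting defines an event as one that "does not necessarily have a cause-and-effect relationship with the intervention". The phrase reads as loose terminology and is not part of this point.

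**Conclusion.** The point holds in a conditional form. The protocol assigns safety to a set whose definition includes a returned efficacy diary, and it defines no treated-only set. This is a rule the document states, so it cannot be set aside as detail left to an analysis plan.

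If an on-treatment diary is meant, which is the reading that gives the clause any effect, a treated participant with a reported event and no returned diary can be excluded from the adverse event results. Event rates can then be biased downward, and possibly unequally between arms. Collection of events is not affected, only which participants are analysed.

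The size is unknown. Over the assumed range of 0 to about 6 lost per arm, the effect runs from nothing to, for example, 34.5% reported as 17.4%. That upper case assumes that all six excluded participants had events and that four of those retained did.

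**What to change.** - In the section Statistical analysis plan, limit the ITT statement to efficacy.
- Add a safety set: all participants who took at least one dose, grouped by treatment received, with no diary condition.
- In the section Intent-to-treat population, state whether the required diary day must fall in the treatment period or may come from the run-in.

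This takes a few sentences and needs no new data, visits or participants. The section Trial status reports that recruitment is under way, so the change should be made and dated before unblinding.
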